## Stepwise Procedure

From month 1 to 6, the following phases have been carried out: (1) development of the work plan for data collection; (2) training course for mental health professionals on the interventions; (3) training course for researchers on assessment tools. From month 7 to 12, patients' recruitment will be implemented. From month 7 to 18, interventions will be provided to participating patients. From month 7 to 20, patients' follow-up assessments are being made. From month 20 to 24, statistical analyses will be performed as well as findings will be disseminated through scientific papers, posters and conference participation. A specific plan for dissemination will be developed, including institutional newsletters, press and media release, flyers, training course throughout the national context in order to promote the implementation of the intervention on a large scale. Moreover, users and carers will be involved in the process of dissemination organizing thematic conferences for presenting the characteristics of the intervention.

The stepwise procedure is summarized in Figure 2.

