## Aims

The present trial aims to evaluate the efficacy and feasibility of a new psychoeducational family intervention compared to the Best Treatment Option (BTO) in a sample of women affected by perinatal depression and their family members. The Best Treatment Option (BTO) is provided according to the NICE guidelines (62). In particular, mild to moderate forms of depression may be addressed with self-help or psychological counseling. For moderate or severe forms of PD, high-intensity psychological intervention, or pharmacological treatments are recommended.

The secondary aims are to: (1) improve mental health literacy on the topic of perinatal depression, with a specific focus on risk and protective factors as well as on available therapeutic strategies for the management of perinatal depression; (2) identify clinical, socio-cultural, and pregnancy-related predictive factors for the development of perinatal depression; (3) improve coping strategies and family functioning of family members participating to the intervention; (4) evaluate the long-term effects of the intervention.

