## Assessment Time and Instruments

Researchers participating to the study are blinded to patient allocation. All patients are assessed at the following time points: baseline (T0); 3 months post-randomization (T1); 6 months post-randomization (T2); 9 months post-randomization (T3); 12 months post-randomization (T4) (Table 2).

**Table 2 T2:** Assessment tools adopted in the study's protocol.

	**Screening phase**	**T0 (baseline)**	**T1 (month 3)**	**T2 (month 6)**	**T3 (month 9)**	**T4 (month 12)**

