## Anticipated Results

### Primary Outcome

The severity of depressive symptoms, evaluating at the HAM-D, has been selected as primary outcome since it is a reliable index and it has already been used in previous studies on the efficacy of psychosocial interventions (84). In particular, the primary outcome is the reduction of at least 50% of the HAM-D scoring at 3 months post-randomization (T1). The work hypothesis is that BTO plus experimental intervention will be more effective than the BTO alone in reducing the severity of depressive symptomatology.

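### The timetable closes follow-up at month 20, but women randomised after month 8 are due their 12-month visit later than that, up to month 24

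*Protocol article*

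**What the plan says.** Under Stepwise Procedure the article gives three windows in project months:

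- recruitment: "From month 7 to 12, patients' recruitment will be implemented";
- follow-up: "From month 7 to 20, patients' follow-up assessments are being made";
- analysis and reporting: "From month 20 to 24, statistical analyses will be performed as well as findings will be disseminated through scientific papers".

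Under Assessment Time and Instruments the visit schedule carries no exception for late recruits: "All patients are assessed at the following time points", namely baseline, then months 3, 6, 9 and 12 after randomisation (T1 to T4). Table 2 marks every instrument except the screening EPDS at all five time points. The Abstract gives the same schedule.

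The primary outcome is assessed at T1 (Primary Outcome; Data Analysis). The fourth secondary aim is to "evaluate the long-term effects of the intervention" (Aims). Power Analysis sets the total at 126 women, allocated 1:1.

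**The concern.** A woman's last visit falls 12 months after her own randomisation, so the final T4 cannot come earlier than 12 months after the last randomisation. With recruitment open until month 12, that is month 24. The timetable ends assessments four months before this and gives the same four months to analysis and dissemination.

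The long-term aim is at stake, because T3 and T4 are the latest data that bear on it. Staff who follow the timetable would stop before many T4 visits are due. Staff who follow the visit schedule would still be collecting data while the analysis runs. A visit that is not made cannot be recovered later, so the conflict should be settled before follow-up closes.

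**Working it through.** **Inputs.** Recruitment in months 7 to 12, follow-up to month 20 and analysis from month 20 (Stepwise Procedure). Visits at 3, 6, 9 and 12 months for all patients (Assessment Time and Instruments, Table 2). Total 126, 1:1, effect size 0.65, α 0.05, power 0.95 (Power Analysis). *Assumption not in the article:* even recruitment over the window.

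**Step 1: the plan's own sample size.** A two-sided two-sample t-test at d = 0.65, α = 0.05 and power 0.95 needs 62.49 per arm, rounded up to 63. Then 2 × 63 = 126, as stated, with power 0.952. The base figure is sound.

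**Step 2: due dates, with no accrual assumption.** Due month = month of randomisation + visit offset.

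| Randomised in month | T1 (+3) | T2 (+6) | T3 (+9) | T4 (+12) |
|---|---|---|---|---|
| 7 | 10 | 13 | 16 | 19 |
| 8 | 11 | 14 | 17 | 20 |
| 9 | 12 | 15 | 18 | **21** |
| 10 | 13 | 16 | 19 | **22** |
| 11 | 14 | 17 | 20 | **23** |
| 12 | 15 | 18 | **21** | **24** |

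Bold entries fall after month 20. All T1 visits (last in month 15) and all T2 visits (last in month 18) fit. T4 fits only for women randomised in months 7 and 8. T3 fails for those randomised in month 12.

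**Step 3: share of women affected, assuming even recruitment.** Let recruitment run from time *s* to *e*, follow-up end at *F*, and the visit fall *v* months after randomisation. The share with the visit due after *F* is (*e* − (*F* − *v*)) / (*e* − *s*). The month labels can be read in three ways:

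| Reading | *s*, *e*, *F* | No T4 (*v* = 12) | No T3 (*v* = 9) |
|---|---|---|---|
| Months counted in full | 6, 12, 20 | (12 − 8)/6 = 67%, 84 women | (12 − 11)/6 = 17%, 21 women |
| Labels as time points | 7, 12, 20 | (12 − 8)/5 = 80%, about 101 women | (12 − 11)/5 = 20%, about 25 women |
| Follow-up stops as month 20 begins | 6, 12, 19 | (12 − 7)/6 = 83%, 105 women | (12 − 10)/6 = 33%, 42 women |

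Two thirds is the lowest of the three. Faster early recruitment would lower the share, and slower early recruitment would raise it.

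**Step 4: illustration of lost precision.** On the first reading, 126 − 84 = 42 women have T4, about 21 per arm. A two-sided t-test at d = 0.65 with 21 per arm has power 0.54. This supposes that an effect of 0.65 holds at 12 months and that nobody drops out. The article claims neither.

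**Step 5: after correction.** With follow-up to the end of month 24, no visit from T1 to T4 falls outside the window.

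**The case against.** **The impact is limited.** The primary outcome is at 3 months, and the last T1 is due in month 15, well inside the window. Sample size, randomisation and the efficacy model are untouched. Data Analysis names no between-arm test at T3 or T4, and Aims does not define long-term. All of this stands, and it keeps the point at moderate severity.

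**The share is not a fact of the plan.** A reader might infer that two thirds of the sample cannot have a T4. The article gives no accrual pattern, so any percentage is conditional and needs a range. What holds without that assumption is the due-date table.

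**There is no power loss against plan.** A reader might also set 0.54 against 0.95. Power Analysis takes 0.65 from an overall effect of psychosocial interventions and does not tie it to month 12, and the efficacy model uses the 3-month HAM-D. The article never promises 0.95 power at T4, so the 0.54 is only an illustration.

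**The visits may still take place.** The article has two conflicting statements, not a rule to stop collecting data, and month 20 may simply be a loose label in a work plan. That is possible, but nothing in the text says that follow-up continues during analysis or that T4 is for early recruits only. Figure 2, which summarises the timetable, is not available in the text reviewed. The stated months are explicit enough to need correcting.

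**Bias between arms.** A reader might suspect it. Truncation by recruitment date applies to both arms alike, so the main harm is lost precision.

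**Conclusion.** The point holds as an inconsistency between the timetable and the visit schedule, of moderate severity. Women randomised after month 8 have T4 due after follow-up closes, and those randomised in month 12 also have T3 due too late. This takes month 20 as counted in full; if follow-up stops as that month begins, the cut-offs come a month earlier. Under even recruitment, which is an assumption, 67% to 83% of women would lack T4 and 17% to 33% would lack T3 if the timetable were followed literally. T1 and T2 are complete on every reading. The consequence is confined to the 9- and 12-month data and the long-term secondary aim. The article does not support reading this as a threat to the primary result.

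**What to change.** Reconcile Stepwise Procedure with Assessment Time and Instruments and Table 2. Change the follow-up line to months 7 to 24, and place the analysis of T3 and T4 after month 24. The primary analysis need not wait for this: it is possible once the last T1 is in, from month 15.

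If month 20 cannot move, state that T4, and T3 for the last recruits, is administratively missing according to recruitment date. Report the 9- and 12-month results as coming from the earlier recruits only, and claim complete follow-up only to 6 months. There is no need to discard T3: on the even-recruitment assumption most women would have it (126 − 21 = 105 on the first reading, 126 − 42 = 84 on the least favourable).

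Cost: about four more months of assessments that are already planned, and a later long-term report. The fallback costs wording only.

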**Figure 2 F2:**
[figure not shown]
Stepwise procedure.

## Anticipated Results

### Primary Outcome

The severity of depressive symptoms, evaluating at the HAM-D, has been selected as primary outcome since it is a reliable index and it has already been used in previous studies on the efficacy of psychosocial interventions (84). In particular, the primary outcome is the reduction of at least 50% of the HAM-D scoring at 3 months post-randomization (T1). The work hypothesis is that BTO plus experimental intervention will be more effective than the BTO alone in reducing the severity of depressive symptomatology.

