## Abstract

Perinatal depression (PD) is a severe and disabling condition impacting negatively on children in terms of adverse neonatal outcomes and on the well-being of women and their families. All pregnant women attending the unit of Gynecology and Obstetrics Service of the University of Campania “L. Vanvitelli” will be screened for PD using the Edinburgh Postpartum Depression Scale (EPDS). Women with a score ≥10 at the EPDS will be invited to receive a full psychiatric assessment. The required sample size is of 126 women with PD which will be randomly allocated to either an experimental group, receiving a uni-familiar psychoeducational intervention, or to a control group, receiving the Best Treatment Option (BTO). Patients will be evaluated through several assessment instruments: Hamilton Depression Rating Scale (HAM-D), Hamilton Anxiety Rating Scale (HAM-A), Global Assessment of Functioning (GAF), Clinical Global Impression (CGI), Manchester Short Assessment of Quality of Life (MANSA), Family Assessment Device (FAD), Family Coping Questionnaire (FCQ), and Pattern of Care Schedule (PCS). Patients will be evaluated at baseline, 3, 6, 9, and 12 months post-randomization. The severity of depressive symptoms at the HAM-D scale has been selected as primary outcome. Other outcome measures include improvement in the severity of anxiety symptoms, of global and personal functioning, an improvement in family members' coping strategies and in the level of quality of life. It has been highlighted the importance of developing screening and treating programs for PD, and our study will use rigorous study design to evaluate the efficacy of the adaption of a well-known family psychoeducational model to the treatment of PD. The aims of present trial are to: (1) develop an informative package for pregnant women with PD; (2) promote a screening programme for PD; (3) identify those (socio-demographic and pregnancy-related environmental) factors associated with a higher risk to develop a perinatal or postnatal depression; (4) evaluate the efficacy of a new experimental psychoeducational intervention in reducing the depressive symptoms during pregnancy compared to the BTO.

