## Statistical analyses

### Power Analysis

In order to assess the efficacy of the experimental intervention, a power analysis was performed. As reported by Sockol et al. (83), available psychosocial interventions for perinatal depression have been found to have an overall effect size of 0.65. Therefore, the sample size has been defined selecting 0.65 as desired level of effect size, an α error set at 0.05 and power set at 0.95. Therefore, the total sample will consist of 126 patients, allocated with a 1:1 ratio to the experimental or to the control group (Figure 1).

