### Data Analysis

Differences in socio-demographic and clinical characteristics, such as severity of depressive and anxiety symptoms, quality of life, trimester of pregnancy, and personal functioning between the two groups will be evaluated using Chi-square or *T*-test for independent samples, as appropriate. Differences in coping strategies and in family accommodation reported by relatives will be evaluated with the same tests.

In order to assess the efficacy of the experimental intervention, a linear multivariable regression model will be implemented, using as main outcome the score at HAM-D at 3 months post-randomization. Moreover, several confounding variables (such as age, marital status, familiarity for mental disorders, peer support, previous pregnancy, etc.) will be entered in the model. Furthermore, predictors of response at the end of the intervention will be identified.

“Response” is generally defined as a 50% decrease in scores on Hamilton Depression Rating Scale (HAMD) (74). In this protocol, we will consider the score at the 3-month HAM-D compared with the baseline score. Therefore, the continuous variable “3-month HAM-D score” will be transformed in a binary variable (1 = response; 0 = absence of response), and it will be entered in a logistic regression multivariate model in order to identify possible predictors of positive response to the experimental intervention.

In order to evaluate differences in relatives' coping strategies according to patients' clinical features and type of relationship with the patient, a two-level model with fixed independent variables and random intercept, using a maximum likelihood estimation, will be performed. The mean score at the subscales of the FCQ will be entered in the model, adding covariates step by step in order to identify the model with indexes of best fit. The final model will be selected according to the−2 loglikelihood value, and the model with the lowest value will be choose. Estimate, standard error, 95% confidence interval, and *P*-values will be calculated.

The level of significance will be set at *p* < 0.05. All analyses will be performed using the Statistical Package for Social Science software (SPSS), version 18.0 (SPSS).

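### The primary outcome is a 50% HAM-D response in one section and the continuous 3-month HAM-D score in another; the sample size and stated power fit only the continuous score

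*Protocol article*

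**What the plan says.** Four parts of the protocol article bear on this point.

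- **Abstract:** "The severity of depressive symptoms at the HAM-D scale has been selected as primary outcome". No threshold is given.
- **Anticipated Results, Primary Outcome:** the opening sentence again names severity on the HAM-D. The next one narrows it: "the primary outcome is the reduction of at least 50% of the HAM-D scoring at 3 months post-randomization (T1". The closing hypothesis returns to severity.
- **Data Analysis:** to assess efficacy, "a linear multivariable regression model will be implemented, using as main outcome the score at HAM-D at 3 months post-randomization". A later paragraph turns the 3-month score into response or no response, relative to baseline, to be "entered in a logistic regression multivariate model in order to identify possible predictors of positive response to the experimental intervention".
- **Power Analysis:** the trial is sized by "selecting 0.65 as desired level of effect size, an α error set at 0.05 and power set at 0.95", giving 126 patients at 1:1. No response rate appears.

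The Discussion describes the main outcome as a reduction of depressive symptoms three months after randomization, without a threshold.

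**The concern.** A mean score and a responder proportion are different outcomes. They have different tests, effect measures and power, and in one data set they can fall on opposite sides of p=0.05. The article calls one of them the primary outcome and the other the main outcome of the efficacy analysis, so a reader cannot tell which result decides the trial.

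Three things follow. The outcome called primary in its own section is given no stated comparison between arms. The power statement is true of one version only. And with both at p<0.05 and no order between them, the choice could be made after the data are seen.

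**Working it through.** **1. Reproduce the plan's figure.** Inputs from Power Analysis: effect size 0.65 (read as a standardised mean difference), alpha 0.05, power 0.95, 1:1 allocation. Sidedness is not stated.

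- Normal approximation, two-sided: n per arm = 2(1.960 + 1.645)² / 0.65² = 61.5, so 62 per arm (124 in total).
- Noncentral t: at 63 per arm the noncentrality is 0.65 × √(63/2) = 3.648, with 124 degrees of freedom and critical value 1.979. Power is 0.952. At 62 per arm it is 0.948. So 63 per arm are needed, which is 126 exactly.
- One-sided, the answer is 52 per arm (104 in total), which does not match.

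The 126 is therefore a two-sided t-test sample size for a continuous outcome.

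**2. Power if response is primary.** The article gives no response rates. I assume a control response p₁ of 20% to 60% and translate the 0.65 effect into a response rate p₂ in two ways:

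- Normal threshold: p₂ = Φ(Φ⁻¹(p₁) + 0.65).
- Logit conversion: odds ratio = exp(0.65 × π/√3) = 3.25, applied to the odds of p₁.

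With p̄ the mean of p₁ and p₂, and Δ their difference:

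- Power = Φ{[Δ√n − 1.96√(2p̄(1−p̄))] / √(p₁(1−p₁) + p₂(1−p₂))}
- n per arm for 0.95 = [1.96√(2p̄(1−p̄)) + 1.645√(p₁(1−p₁) + p₂(1−p₂))]² / Δ²

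Example, p₁ = 0.40, normal threshold: p₂ = 0.654, Δ = 0.254, p̄ = 0.527. The power argument is (0.254 × 7.937 − 1.96 × 0.706) / 0.683 = 0.925, so power is 0.82. For 0.95, n = (1.384 + 1.123)² / 0.254² ≈ 97.4, so 98 per arm.

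| Control response | p₂, normal | Power at 63 | n per arm for 0.95 | p₂, logit | Power at 63 | n per arm for 0.95 |
|---|---|---|---|---|---|---|
| 20% | 42.4% | 0.78 | 109 | 44.8% | 0.85 | 90 |
| 30% | 55.0% | 0.82 | 99 | 58.2% | 0.90 | 78 |
| 40% | 65.4% | 0.82 | 98 | 68.4% | 0.90 | 77 |
| 50% | 74.2% | 0.81 | 102 | 76.5% | 0.88 | 84 |
| 60% | 81.7% | 0.77 | 112 | 83.0% | 0.82 | 98 |

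Between the tabled rates the logit power peaks at 0.905, near a 35% control response, hence an upper end of 0.91.

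**3. Difference that 63 per arm can detect with 0.95 power.** About 30 percentage points: 20% vs 50%, 30% vs 61%, 40% vs 71%, 50% vs 80%. The 0.65 effect corresponds to about 22 to 25 points (normal) or 23 to 28 points (logit).

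**4. Two candidate primaries.** I simulated trials with no treatment effect: 63 per arm; baseline mean 18, SD 4; 3-month mean 10, SD 6; baseline to 3-month correlation 0.2, 0.4 or 0.6; 10,000 trials each. None of the means, SDs and correlations comes from the article. A t-test on the 3-month score or an uncorrected two-proportion test on response was significant in 8.3% to 8.6% of trials. The response test alone ran slightly above nominal (5.4% to 5.8%), so a small part of the excess is its own.

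**The case against.** The strongest reply is that the plan does have a primary outcome, the continuous score, and that one loosely worded sentence does not displace it. The Abstract, the opening and closing sentences of Primary Outcome, the efficacy sentence of Data Analysis and the Discussion all lean towards severity. On that reading 126 and 0.95 are right. This stands, and it rules out a stronger reading that a reader might infer: that the trial is underpowered. The shortfall exists only if the responder sentence governs.

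A second stronger reading is that response cannot be compared between arms under this plan. The article does not list the logistic model's terms, and an article may leave that list to a fuller plan. Treatment arm is not named as a term in the linear model either; it is inferred from that model's stated purpose, which is efficacy. What can be said is that the logistic model's stated purpose is "in order to identify possible predictors of positive response to the experimental intervention" and that no arm comparison of response is specified.

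Third, the power figures for response rest on assumed rates and conversions. Power of 0.95 is not out of reach for a responder outcome; it would take a difference of about 30 points. This too stands.

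The reply does not remove the contradiction. The narrowing sentence explicitly calls the 50% reduction the primary outcome, and neither condensation into an article nor an unseen analysis plan explains two different definitions in one document.

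**Conclusion.** The concern holds as an internal contradiction over the primary outcome, and it should be corrected. The sample size and the 0.95 power fit the continuous 3-month HAM-D score (power 0.952 at 63 per arm, two-sided, all patients evaluable).

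If the 50% response governs, the stated power is unsupported. Within the assumed 20% to 60% control response, it is about 0.77 to 0.82 (normal threshold; 98 to 112 per arm needed for 0.95) or 0.82 to 0.91 (logit; 77 to 98 per arm). That power falls when the score is dichotomised is firm for an equivalent effect; the amount depends on those assumptions.

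The false-positive chance of about 8% to 9% with two unranked candidates is illustrative. Only its direction, above 5%, carries over to this trial.

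**What to change.** - **Primary Outcome:** name one primary outcome, the HAM-D total score at 3 months (T1), compared between arms by the linear model of Data Analysis. List the reduction of at least 50% as a secondary outcome.
- **Data Analysis:** give response its own between-arm comparison, as a difference in responder proportions with a 95% confidence interval, separate from the search for predictors.
- **Power Analysis:** state that the 0.95 refers to the continuous T1 score, two-sided, with all 126 patients evaluable.

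If the sponsor wants response to stay primary, Data Analysis must specify its between-arm test, and Power Analysis must replace 0.95 with the power for 63 per arm recalculated from response rates that the sponsor states. The ranges above should not be copied in, since they rest on assumed rates.

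Either route changes wording only and needs no extra patients or data. Under the preferred route the responder result becomes secondary.
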